#### 9.4.4 SAFETY ANALYSES

##### Triggers for ad hoc review

Serious Adverse events that result in participant death will trigger ad hoc review, which will take place between the DSMB, the Coordinating Center and the involved Performance Site via conference call

##### Stopping Rules

Human subjects recruitment will cease if the University of Michigan IRB or NIAMS, based on the recommendation from the DSMB, determine that there is an unacceptable number of adverse events, if the serious, related adverse event rates differ between the two study groups at an alpha level of 0.05 at each time when side effects are assessed for DSMB report, or if it becomes apparent that during the planned 2.5 years of participant recruitment, we will achieve less than 25% of our recruitment goal.

---

#### 9.4.5 BASELINE DESCRIPTIVE STATISTICS

We will compare the three groups to ensure reasonable similarity in their baseline characteristics using analysis of variance for continuous variables such as age, and chi-square test for categorical variables such as sex. Because the sample size is fairly large, we do not expect clinically meaningful baseline imbalances, but we will include baseline variables showing differences across the groups with  $p < 0.15$  as potential covariates in the primary analysis.

---

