| SF-36                                                                                                                                                               |           | ✓          |         | ✓               | ✓                 | ✓                   | ✓                   | ✓                    | ✓                    |
| Pain Domain of MHQ                                                                                                                                                  |           | ✓          |         | ✓               |                   |                     |                     |                      |                      |
| Surgery Data Form                                                                                                                                                   |           |            | ✓       |                 |                   |                     |                     |                      |                      |
| General Health Questionnaire                                                                                                                                        |           |            |         | ✓               | ✓                 | ✓                   | ✓                   | ✓                    | ✓                    |
| Fingertip to Palmar Crease Distance Form                                                                                                                            |           |            |         | ✓               | ✓                 |                     |                     |                      |                      |
| Complication Checklist                                                                                                                                              |           |            |         | ✓               | ✓                 | ✓                   | ✓                   | ✓                    | ✓                    |
| Hand Therapy Data Form                                                                                                                                              |           |            |         | ✓               | ✓                 | ✓                   | ✓                   | ✓                    | ✓                    |

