| MHQ (All Domains)                                                                                                                                                   |           |            |         |                 | ✓                 | ✓                   | ✓                   | ✓                    | ✓                    |
| Hand Function Data Form                                                                                                                                             |           |            |         |                 | ✓                 | ✓                   | ✓                   | ✓                    | ✓                    |
| Participant Payment                                                                                                                                                 |           | ✓          |         | ✓               | ✓                 | ✓                   | ✓                   | ✓                    | ✓                    |
| Adverse Event Collection (if necessary)                                                                                                                             |           | ✓          | ✓       | ✓               | ✓                 | ✓                   | ✓                   | ✓                    | ✓                    |
| Protocol Deviation Collection (if necessary)                                                                                                                        |           | ✓          | ✓       | ✓               | ✓                 | ✓                   | ✓                   | ✓                    | ✓                    |
| RAPA = Rapid Assessment of Physical Activity; MHQ = Michigan Hand Outcomes Questionnaire; SF-36 = Short-Form 36 Questionnaire; MMSE = Mini Mental State Examination |           |            |         |                 |                   |                     |                     |                      |                      |

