**Aim 2:** To compare the recovery trend for elderly DRFs treated with VLPS with CRP and EFP.

*Rationale:* The rate of recovery for these three treatment methods is unknown. Patients will be assessed at 2 weeks, 6 weeks, 3 months, 6 months, 12 months and 24 months after surgical treatment to determine which treatment method provides the most rapid recovery.

*Hypothesis:* Patients treated with VLPS will have better outcomes at earlier times than those treated with the more conservative techniques, and the better outcomes will persist at the 24-month period.

**Aim 3:** To determine predictors of outcomes after surgical treatment of DRFs in the elderly.

*Rationale:* Predictors of functional outcomes in the elderly have not been studied. We will evaluate predictors of outcomes based on demographic characteristics, fracture patterns and treatment types.

*Hypothesis:* Severity of fracture, adequacy of reduction, bone mineral density, preinjury functional status and patient socioeconomic status are predictors of functional outcomes after treatment.

**Aim 4:** To compare the 12-month post-surgical outcomes and 24-month recovery trends of patients who have chosen not to have surgery with patients within the surgical arm.

*Rationale:* Elderly patients may have low functional demands, and it has been postulated that they can tolerate the deformity that almost certainly results following treatment with closed reduction and casting only.

*Hypothesis:* Patients treated with surgery will have better outcomes earlier than those treated nonsurgically.

**Aim 5:** To conduct a cost-utility analysis comparing the three treatment arms with the nonsurgical arm.

*Rationale:* A formal economic analysis comparing the three treatment options for DRFs has not been performed. We will evaluate cost and patient preferences to arrive at a dominant strategy.

*Hypothesis:* Although VLPS is more costly, earlier functional gains makes this treatment a dominant strategy.

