#### ***Procedure for Randomizing a Participant***

Randomization should only be performed once all eligibility criteria have been assessed (Section 5) and the Inclusion/Exclusion form and the Mini Mental Status Exam (MOOP Section Q2) have been completed. Patients must provide informed consent form prior to randomization as well. The participant should be randomized to receive one of the three fixation techniques as soon as possible so that he/she may schedule surgery, receive pre-operative instructions and have any questions answered.

A Research Coordinator at each Clinical Site will login to the Treatment Assignment Tool – University of Michigan (TATUM) website (<https://michrapps.med.umich.edu/tatum/>) with their UM uniusername/username and Level 1 password (or UM Friend Account email and Level 1 password). Please enter the participant's StudyID and click "Retrieve Treatment" and "Okay" to confirm that you wish to randomize a participant. A screen will appear with the participants StudyID, Randomized ID and the Treatment Group. (See MOOP Appendix 5 for TATUM User Guide) Please record this information for entry in REDCap in the Study Arm form. An automatically generated email will be sent to the Coordinating Center and to the Clinical Site. Once the randomization assignment has been retrieved, the researcher will notify the surgery scheduler and record this information in the participant's study file.

The surgery scheduler should make every attempt to schedule the procedure without the surgeon knowing the exact procedure to be performed. Methods for doing this will vary from site to site; at the University of Michigan this will be achieved by scheduling the procedure as a "WRIST distal radius fixation." Surgical staff will prepare materials for each of the three procedures. No more than 24 hours before the procedure the surgeon should be informed of which procedure the patient was randomized to. This should be done using 2 methods, in case one method fails. These methods may include presenting an envelope to the surgeon, email, text message, or contacting the surgery scheduler to reveal the procedure in the schedule.

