### 9.4.2 ANALYSIS OF THE PRIMARY EFFICACY ENDPOINT(S)

**Aim 1:** *To compare 12-month post-surgical outcomes of elderly DRFs treated with VLPS with CRP and EFP.* Primary outcome will be the summary score of the MHQ. We will report means for each group and the mean difference between pairs of each group, along with their 95% confidence intervals. The primary outcome will be compared using a linear mixed-effects model to address the hierarchical nature of the data. The model will include surgeons nested within site and sites as random effects, fracture severity group indicator effect and two indicators for EFP and CRP groups. The surgical procedure indicators will each estimate the difference between EFP to VLPS and CRP to VLPS. We will also obtain covariate adjusted estimates of the between group differences; the covariates will be determined by the baseline analyses and will likely include age, baseline MHQ score, dominance of the injured hand and baseline RAPA score. Similar analyses will be done using other secondary outcome variables, including grip strength. We will also calculate MHQ score and grip strength as the difference (and %) of the uninjured hand scores. These measures may better reflect recovery because the uninjured hand can give a proxy measure of the patient-specific maximum achievable outcome. Analysis of complications will depend on how often they occur. For example, if the combined complications are rare, we will dichotomize them as present/absent and use a generalized linear mixed-effects model with logit link to compare the odds of complication between VLPS/EFP and between VLPS/CRP, while adjusting for within surgeon and site correlation. If the number of complications is substantial, we will use a count data model such as generalized linear model with log link to make the between-group comparison.

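### Covariates for the adjusted MHQ comparison are chosen by baseline p < 0.15 tests rather than fixed on prognostic grounds, and one of those listed, the baseline MHQ score, cannot be formed from the scheduled data

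*Protocol*

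**What the plan says.** Section 9.4.5 compares the three surgical arms at baseline by analysis of variance or chi-square test. It then says "we will include baseline variables showing differences across the groups with" p < 0.15 "as potential covariates in the primary analysis".

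Section 9.4.2 sets out a mixed model for the 12-month MHQ summary score with surgeon and site random effects, a fracture severity indicator and two arm indicators. Covariate-adjusted estimates are presented as an addition to it, for which "the covariates will be determined by the baseline analyses and will likely include age, baseline MHQ score, dominance of the injured hand and baseline RAPA".

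In the Schedule of Activities (Section 1.3) the row "Pain Domain of MHQ" is ticked at enrolment and 2 weeks. The row "MHQ (All Domains" is first ticked at 6 weeks. Section 8.1.3 also lists only the pain domain among the baseline assessments.

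Section 9.2 expects covariate adjustment to raise power when the covariates are associated with the outcome.

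**The concern.** Randomisation makes every true baseline difference between arms zero, so a test of baseline difference carries no information on whether a variable predicts the outcome. A screen built on it admits irrelevant variables and drops strong predictors that happen to be balanced. It therefore does not serve the purpose Section 9.2 gives for adjusting. Because those that pass are only potential covariates, a second choice remains after the data are seen. What is at stake is the precision and reproducibility of the adjusted comparison of VLPS with CRP and with EFP.

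Separately, the listed covariate closest to the outcome, a baseline score on the same instrument, has no scheduled data behind it.

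**Working it through.** **1. The plan's own sample size (Section 9.2).** Inputs: difference 8, SD 18, two-sided alpha 0.025, power 80%, 24 patients per site, ICC 0.012, 20% loss.

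- Per arm without clustering: 2 × (2.2414 + 0.8416)² × 18² / 8² = 96.2, rounded up to 97; 98 with the t distribution.
- Design effect: 1 + (24 − 1) × 0.012 = 1.276.
- 98 × 1.276 = 125.05, rounded up to 126. Then 126 / 0.80 = 157.5, rounded up to 158.
- Power at 126 per arm: 0.811 (0.805 with the t distribution).

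The stated 126 and 158 reproduce. They assume no reduction in SD from covariates.

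**2. What the screen selects.** Each variable passes with probability 0.15. For k independent variables (k and independence are assumptions), the expected number selected is 0.15k, and the chance of at least one is 1 − 0.85^k.

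| k | Expected selected | Chance of at least one |
|---|---|---|
| 4 | 0.6 | 0.48 |
| 10 | 1.5 | 0.80 |
| 20 | 3.0 | 0.96 |

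A given prognostic variable is missed with probability 1 − 0.15 = 0.85.

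**3. What that costs.** Let R² be the outcome variance explained by one covariate beyond fracture severity. The protocol gives no value, so 0.10 to 0.30 is an assumed range, and 18 is taken as the SD before that covariate enters. With the covariate fixed in advance, the residual SD is 18 × √(1 − R²).

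The rule itself was simulated: three arms of 126, SD 18 × √1.276 = 20.3 to carry the design effect, and adjustment only when the three-arm analysis of variance gave p < 0.15. There were 20,000 runs with no difference and 8,000 with an 8-point difference.

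| Extra R² (assumed) | Power by formula, covariate fixed | Simulated, never adjusted | Simulated, p < 0.15 rule | Simulated, always adjusted | Type I error of the rule (nominal 0.025) |
|---|---|---|---|---|---|
| 0.10 | 0.853 | 0.815 | 0.825 | 0.856 | 0.022 |
| 0.20 | 0.894 | 0.811 | 0.830 | 0.897 | 0.021 |
| 0.30 | 0.932 | 0.807 | 0.835 | 0.930 | 0.018 |

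Power forgone against always adjusting is 0.856 − 0.825 = 0.031, 0.897 − 0.830 = 0.067 and 0.930 − 0.835 = 0.095. The rule's type I error is slightly below nominal, because in the balanced trials it keeps the unadjusted, larger standard error.

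**4. Baseline MHQ.** Sections 1.3 and 8.1.3 agree that only the pain domain is taken at enrolment. Section 10.1.6.2 says loosely that forms including the MHQ are collected at every visit. The same sentence lists the RAPA, which Section 1.3 schedules only at enrolment and 24 months, so it cannot be read as adding a full MHQ at enrolment.

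**The case against.** The best defence is that Section 9.4.2 already fixes a base model containing fracture severity and treats adjustment as additional. It also names age, hand dominance and RAPA as likely covariates before any test is run. A final covariate list is commonly left to a SAP, which was not available here. Much of this stands: prognosis is not ignored, and for any named variable that enters regardless of the screen, less is forgone than in the table.

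It does not remove the point. The protocol does more than leave the list open: it states a selection rule, and the rule is a poor one. None of the three named variables is committed to. Section 9.4.5 places the selected variables in the primary analysis while Section 9.4.2 places them beside it, so the status of the adjusted model is unsettled.

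Stronger readings that a reader might infer are not supported:

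- **Inflated type I error.** The simulation shows 0.018 to 0.022 against 0.025.
- **An underpowered trial.** The sample size takes no credit for covariates, and its 80% reproduces.
- **A saving worth 11% to 43% more patients.** This is 1/(1 − R²) − 1 at R² of 0.10 and 0.30. It needs the increment over fracture severity, which the documents do not give.
- **No baseline MHQ data at all.** The pain domain is collected; only the summary score is missing.
- **Covariates measured after randomisation.** Section 1.3 ticks randomisation at Visit 1 and the baseline questionnaires at Visit 2, but Section 6.3 says "Randomization should only be performed once all eligibility criteria have been assessed" and the MMSE is complete. This is a discrepancy in the schedule, not evidence of conduct.

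**Conclusion.** The point holds in this limited form. The p < 0.15 rule selects covariates by chance and should be replaced, and one listed covariate, the baseline MHQ summary score, cannot be formed from the scheduled assessments. The harm is an avoidable loss of precision and an adjusted estimate that can vary with chance and with the analyst.

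Its size depends on assumptions. For one screened covariate with an extra R² of 0.10 to 0.30, about 3 to 10 percentage points of power are forgone. If the covariates add little beyond fracture severity, the loss is small. If the adjusted model is only supporting, the loss falls on that analysis and the base model keeps power of about 0.81.

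Two minor discrepancies are separate from this. Aim 3 hypothesises that "bone mineral density, preinjury functional status and patient socioeconomic status are predictors of functional outcomes", and bone mineral density recurs in the predictor lists of Sections 9.4.3 and 9.4.7, yet it appears on no scheduled activity or listed form. The form list is not exhaustive and the manual of procedures was not available, so it cannot be said that the measure is collected nowhere. The other is the order of randomisation and MMSE in Section 1.3 against Section 6.3.

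**What to change.** 1. Delete the p < 0.15 selection rule from Section 9.4.5 and keep the baseline tables descriptive.
2. In Section 9.4.2, fix one covariate-adjusted model on prognostic grounds from variables already collected: fracture severity, age, dominance of the injured hand, enrolment RAPA and enrolment MHQ pain domain.
3. Replace the baseline MHQ score with the enrolment pain domain, and correct the loose sentence in Section 10.1.6.2.
4. State in both sections whether the adjusted model is the primary or a supporting analysis.
5. As minor reconciliations, state the source of bone mineral density or remove it from Aim 3 (Sections 4.1, 9.1, 9.4.3 and 9.4.7), and align the randomisation tick in Section 1.3 with Section 6.3.

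The cost is wording only, with no new data. Section 10.3 dates the current version 04/03/18, ahead of manuscript submission, so the change should be dated and should say whether outcomes by arm had been seen. If they had, the adjusted model should not be called prespecified.

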#### 9.4.6 PLANNED INTERIM ANALYSES

Not applicable.

---

#### 9.4.7 SUB-GROUP ANALYSES

**Aim 3:** *To determine predictors of outcomes after surgical treatment of DRFs in the elderly.* We will assess the effect of potential predictors of outcomes within each surgical treatment group and assess whether the effect remains the same across the treatment groups. Potential predictors are variables found to be associated with post-surgical outcomes in our previous studies and include fracture severity, reduction adequacy (measured, for example, using intra-articular step-off for intra-articular fractures), age, income level, baseline activity level and bone mineral density. The analysis will initially be done separately in the three surgical groups using the linear mixed-effects models and 12-month outcomes. Other variables potentially associated with outcome variation are pre-existing arthritis, extensive soft-tissue injury, presence of nerve injury, presence of other associated injuries and whether the dominant hand is injured. Although some of the proposed potential predictors are likely to be collinear, we do not have two variables that are highly collinear on face value. We will, however, assess multi-collinearity and employ data reduction strategies to reduce the number of variables. In a separate model, we will also consider 6-week values of the outcome variable as a potential predictor of long-term outcome. Within each surgical group, other variables will be considered such as an indicator for additional fixation requirement using additional plates or screws as a part of the VLPS placement, because the added fixation procedures may indicate a more severe fracture pattern. For continuous

variables such as age, we will explore a proper functional relationship using age categorical indicators and splines. If the models for each surgical group show similar relationships between predictors and outcome variables, we will combine the data across the surgical groups. We do not have a hypothesized differential effect of a predictor on outcomes that depend on surgical group, and thus interactions will be explored only if a large difference in the relationship between a predictor and outcomes are observed between any two surgical groups. Similar analyses will be done using secondary outcome variables of interest.

---

#### 9.4.8 TABULATION OF INDIVIDUAL PARTICIPANT DATA

Not applicable.

---

#### 9.4.9 EXPLORATORY ANALYSES

Aim 5: To conduct a cost-utility analysis comparing the three treatment arms with the nonsurgical arm. To calculate QALYs for a cost-utility analysis, we have already begun development and initial testing of an online time trade-off (TTO) survey to determine utility for various health states related to DRF. Utility is the preference assigned to a particular health state on a scale where 0 represents death and 1 represents perfect health. Using the TTO method, a person is asked to choose how much time in his/her life he/she is willing to give up to be in a healthier state while avoiding a less healthy one. We will assess the utilities for different health states that could occur (malunion, nonunion, infection, etc) following DRF treatment. Data from the current study will be used to determine the outcomes and complications of DRFs. QALYs will then be calculated from the utilities, adjusted for years of life remaining for different age groups. We will also obtain utilities of elderly subjects from the community for a comprehensive analysis of the societal perspective, as recommended by the Panel on Cost Effectiveness in Health and Medicine. Medical costs will be assessed using the relevant charges/cost data for the procedures on all participants recruited at the Michigan Medicine . The costs of lost productivity will be valued as the average US hourly wage, as obtained from the US Bureau of Labor Statistics, of a person most likely to be affected by a DRF, multiplied by the average time to healing, as obtained from this study. Costs will be discounted at a rate of 3%. Sensitivity analyses will be done to change the assumptions to fit the extremes of these estimates. If, in changing these estimates, the results are similar, we can be assured of the stability of the conclusions. One- and two-way sensitivity analyses will be performed to determine the stability of the incremental cost-utility ratio, which will incorporate the cost and utility range of the study subjects' in the calculations

